## 2. Stepped-care for anxiety/depression

Dizzy older patients with the risk factor 'anxiety and/or depression' (defined as the presence of Generalised Anxiety Disorder (GAD), Panic Disorder (PD), or Major Depressive Disorder (MDD)), will follow a stepped-care program, according to the Trimbos Multidisciplinary Guideline Anxiety Disorders and the Trimbos Multidisciplinary Guideline Depression. The presence of GAD/PD/MDD will be assessed by the and GAD-7, Patient Health Questionnaire, panic module (PHQ-PD), and the PHQ-9 (see next paragraph). Stepped-care has been proven to be effective in older people with anxiety and/or depression.

Stepped-care involves four subsequent treatment steps for anxiety and depression in primary care. A practice nurse mental health (POH-GGZ) of the patient's own general practice guides the patient through the various steps of the program. All participating POH's-GGZ will receive a training of two days about stepped-care, guided self-help and problem solving therapy before start of the intervention. The GP is easily accessible for the POH-GGZ to discuss about a patient if needed. The steps of the program involve: (1) watchful waiting, 6 weeks; (2) bibliotherapy, 6 weeks; (3) Problem Solving Therapy, 6 weeks; and (4) indicated treatment. The patient will proceed to the next step after every 6 weeks in case of persisting complaints. The POH-GGZ will seek for an alternative treatment step if a patient is not motivated for an offered intervention. The intervention, as part of our study, is finished when the patient does not suffer from anxiety/depression anymore, or when the patient still suffers from anxiety/depression and proceeds to step 4.

*Step 1. Watchful waiting.* The first 6 weeks consists of a period of watchful waiting, because it is known that depressive/anxiety symptoms often disappear spontaneously over time. In this 6 week period, the patient will be invited by the POH-GGZ for a first consultation to get familiar with the POH-GGZ. During this introductory consultation the POH-GGZ will shortly inform the patient about depression/anxiety and the stepped-care program. After 6 weeks the POH-GGZ will invite the patient again. The patient will be asked to fill out the GAD-7, PHQ-PD and PHQ-9. In case of persisting anxiety and/or depression the patient will go to step 2.

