### 3. Exercise therapy for risk factor impaired functional mobility

Dizzy elderly with the risk factor 'impaired functional mobility' (defined as a TUG score of 20 seconds or more), will receive standardized exercise therapy by a physiotherapist. Earlier research has shown that exercise therapy aiming to improve strength and balance in older people has a positive effect on mobility and reduces rate of falls and risk of falling. The exercise therapy implies training in a group session of one hour twice a week for eight weeks and will focus on strength (including resistance) and balance.

The program starts with 15 minutes warming up exercises in standing and walking with different combinations of head, trunk, arm and leg movements. This will be followed by a circuit training with 8 stations. The patients will perform a two minute exercise at every

station and will perform two laps of the circuit. The stations include the following exercises: standing on foam with eyes closed, standing on foam while flexing the knees and turning the head from side to side, a walking exercise with slalom between cones, knee flexor/extensor training with an ankle cuff, hip abductor/adductor training with an ankle cuff, standing up on toes, and standing on heels. All exercise of the circuit will be individually tailored by performing the exercises with or without extra support to remain standing, varying with the weight of the ankle cuff, standing or walking on heels and toes and standing or jumping on the trampoline. The exercise therapy will end with a cooling down of 10 minutes. The program will be accompanied by music of the group's preference.

No adverse reactions other than musculoskeletal discomfort related to exercise therapy has been described, in particular no fall related injuries occurring during exercise programs have been described.

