### 8.3 Study procedures

#### Questionnaires

If a patient agrees to participate in the study he/she will receive a set of questionnaires. Patients in group A (n = 125) will receive three questionnaires at baseline and at 6 and 12 months follow-up. Patients in the intervention study (group B and C, n = 250) will receive four questionnaires at baseline and at 3, 6 and 12 months follow-up. The questionnaires will be discussed later in this section.

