### Outcome measures

#### Questionnaires

- Dizziness handicap inventory (DHI).

Time to fill out: 10 minutes.

The DHI is a widespread used self-report questionnaire, designed to quantify the impact of dizziness on everyday life. The DHI has 25 items with 3 answer categories ('yes', 'sometimes', or 'no'), investigating self-perceived physical, emotional, and functional disability associated with dizziness. DHI scores range from 0-100. A higher DHI score indicates a higher level of dizziness-related impairment. A DHI score of  $\geq 30$  correlates with current significant impairment because of dizziness.

- Dizziness handicap inventory, short version (DHI-S).

This is a short screening version of the DHI, in which 10 items of the original DHI are extracted. The 10 items in the DHI-S are scored are also scored in 3 answer categories ('yes', 'sometimes', or 'no'). A DHI score of  $\geq 12$  correlates with current significant impairment because of dizziness.

- Generalised Anxiety Disorder-7 (GAD-7).

Time to fill out: 5 minutes.

The GAD-7 is a 7-item questionnaire to identify GAD. Scores on the GAD-7 range from 0 to 21; scores of 5, 10, and 15 represent mild, moderate, and severe anxiety symptoms, respectively.

- Patient Health Questionnaire, panic module (PHQ-PD).

Time to fill out: 5 minutes.

The PHQ-PD will enable us to determine the presence of PD. The diagnostic algorithm for PD consists of 15 questions with 2 answer categories (yes or no) and is considered fulfilled if the answer to questions 3a-d is "yes" and if the answer to 4 or more of questions 4a-k is "yes".

- 9-item Patient Health Questionnaire depression module (PHQ-9).

Time to fill out: 5 minutes.

The PHQ-9 is designed to detect depression. The PHQ-9 has 9 questions with a score ranging from 0 to 3 for each question (maximum score of 27). A threshold score of 10 or higher is considered to indicate mild MDD, 15 or higher indicates moderate MDD, and 20 or higher severe MDD.

- Euro Quality of Life–5-dimension, 5-level (EQ-5D-5L).

Time to fill out: several minutes.

The EQ-5D-5L is a questionnaire that defines health in five dimensions (mobility, self-care, usual activities, pain/discomfort, anxiety/depression) and is often used to translate the effect of an intervention into Quality Adjusted Life Years (QALY's).

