### 10.2 Secondary study parameter(s)

Presence of anxiety/depression, quality of life, dizziness frequency, fall incidence and health care utilization will be taken along in the univariate and multivariate analysis as stated above.

The economic evaluation will be analysed according to the intention-to-treat principle. Costs typically have a highly skewed distribution. Therefore, bootstrapping with 5000 replications will be used to calculate 95% confidence intervals around the mean difference in total costs between the treatment groups. The effect measure that will be used for the cost-effectiveness is EQ-5D-5L. Incremental cost-effectiveness ratios (ICERs) will be calculated by dividing the difference in mean total costs between the

treatment groups by the difference in mean effects between the treatment groups. Bootstrapping will be used to estimate the uncertainty surrounding the ICERs which will be graphically presented on cost-effectiveness planes. Cost-effectiveness acceptability curves and net monetary benefits will also be calculated. Cost-effectiveness acceptability curves show the probability that the intervention is cost-effective in comparison with usual care for a range of different ceiling ratios thereby showing decision uncertainty.

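### The EQ-5D-5L, the effect measure of the cost-effectiveness analysis, is left off the 3-month questionnaire that groups B and C already receive; if effects are expressed as QALYs, months 0 to 6 rest on a straight line between two points

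*Protocol*

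**What the plan says.** Cost-effectiveness is the third secondary objective (section 2), and quality of life by EQ-5D-5L is the first secondary outcome listed in section 8.1.2. For the economic evaluation, section 10.2 states: "The effect measure that will be used for the cost-effectiveness is EQ-5D-5L". The ICER divides the between-arm difference in mean total costs by the difference in mean effects. Section 10.2 does not say whether the effect is a QALY area or a change score. Section 8.3 says that the instrument "is often used to translate the effect of an intervention into Quality Adjusted Life Years (QALY's".

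On timing, section 8.3 says that groups B and C "will receive four questionnaires at baseline and at 3, 6 and 12 months follow-up". In the overview of measurements in the same section, the intervention-study columns mark the DHI, PHQ-9, GAD-7 and PHQ-PD at all four times. The EQ-5D-5L row is marked at baseline, 6 and 12 months, with the 3-month cell empty. No reason is given. For the burden of the form, section 8.3 gives: "Time to fill out: several minutes".

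The scheduled treatment (section 5.1) is concentrated early:

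- Exercise is "training in a group session of one hour twice a week for eight weeks".
- Medication review is a monthly meeting, followed by a GP consultation within two weeks.
- Stepped care consists of "1) watchful waiting, 6 weeks; (2) bibliotherapy, 6 weeks; (3) Problem Solving Therapy, 6 weeks; and (4) indicated treatment". As a study intervention it ends on recovery, or "when the patient still suffers from anxiety/depression and proceeds to step 4".

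**The concern.** The effect side of the ICER is observed less often than the clinical scales, and the missing observation falls inside the treatment period. A QALY computed from values at 0, 6 and 12 months assumes that the between-arm difference moves in a straight line from baseline to month 6. If it rises early and fades, or appears late, the incremental QALY is misstated. The ICER, net monetary benefit and acceptability curve inherit that error.

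The gap cannot be closed afterwards. The measurement schedule is fixed in the protocol, and an analysis plan cannot recover a form that was never sent. The multiple imputation planned in section 10 would have no observed 3-month EQ-5D-5L value in any patient to work from. The bootstrap in section 10.2 describes sampling error and would not show an interpolation error.

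**Working it through.** **Inputs from the protocol.** EQ-5D-5L at 0, 6 and 12 months, and mailings at 0, 3, 6 and 12 months (section 8.3). Exercise 8 weeks; medication review up to one month plus two weeks; stepped-care steps 1 to 3 at 6 weeks each (section 5.1). The protocol gives no utility values, so the utility paths below are assumptions. It also gives no QALY figure that could be reproduced first.

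**Timing.** With 52.18/12 = 4.35 weeks per month, 3 months is about week 13 and 6 months about week 26. Counted from baseline with a prompt start:

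- medication review and consultation: 4.35 + 2 = about week 6
- exercise: week 8
- stepped-care steps 1 to 3: 6 + 6 + 6 = week 18 (week 19 if the maximum of seven problem-solving sessions is weekly)

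These activities therefore fall within months 0 to 6. At month 3 the first two are over and stepped care may still be running.

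**QALY weights.** Let d0, d3, d6 and d12 be the between-arm utility differences, with time in years.

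- Visits at 0, 0.25, 0.5 and 1: area = 0.125 d0 + 0.25 d3 + 0.375 d6 + 0.25 d12
- Visits at 0, 0.5 and 1 (as planned): area = 0.25 d0 + 0.5 d6 + 0.25 d12
- Four-point minus three-point area: 0.25 d3 - 0.125 d0 - 0.125 d6 = 0.25 x [d3 - (d0 + d6)/2]

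The difference is zero exactly when the month-3 value lies midway between the baseline and month-6 values.

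**Assumed paths**, with d0 = 0 and the largest difference equal to d:

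| Path (d3, d6, d12) | With month 3 | As planned | Error of the plan |
|---|---|---|---|
| Linear rise to month 6, then flat (0.5d, d, d) | 0.125d + 0.375d + 0.25d = 0.750d | 0.750d | 0 |
| Present from month 3, sustained (d, d, d) | 0.25d + 0.375d + 0.25d = 0.875d | 0.750d | -14% |
| Half left at months 6 and 12 (d, 0.5d, 0.5d) | 0.25d + 0.1875d + 0.125d = 0.5625d | 0.375d | -33% |
| Half left at month 6, none at 12 (d, 0.5d, 0) | 0.25d + 0.1875d = 0.4375d | 0.250d | -43% |
| Nothing until after month 3 (0, d, d) | 0.375d + 0.25d = 0.625d | 0.750d | +20% |

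In absolute terms, with an assumed d of 0.05, the fourth path gives 0.0219 against 0.0125, a gap of 0.0094 QALY. The four-point area is itself an interpolation, so it is a closer approximation and not the true value.

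**The case against.** The passages do not contradict one another. Baseline, 6 and 12 months is the same EQ-5D-5L schedule as in the validation study and spans the whole year. The strongest objection concerns the effect definition: section 10.2 names the instrument but no area under the curve. If the effect is a 12-month change score, the 3-month value never enters. That stands, and the point is conditional on QALYs for this reason.

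Several stronger readings are tempting, and the documents do not support them:

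- **That all treatment is over before the first EQ-5D-5L follow-up.** Scheduled activity would be, given a prompt start, but no waiting time is stated. Medication adjustment, expected in 62% of the intervention group, can produce drug changes that persist. Step 4 care can also run past 6 months, although it lies outside the study intervention.
- **That an early peak is the likely course.** Stepped care (an expected 48%) opens with six weeks of watchful waiting and is mid-programme at month 3. A gradual build-up is at least as plausible, and if it is linear to month 6 there is no error.
- **That costs are counted in full while effects are missed.** One year of cost collection is a reasonable inference from total costs, record extraction and one-year follow-up, but no cost window is stated. Consultations and admissions can accrue all year.
- **That the ICER would be 1.75 times too high.** The ratio 0.0219/0.0125 gives that figure only for one assumed path, with a positive and unchanged cost difference. The introduction expects a cost reduction.
- **That the direction of error cannot be checked.** The DHI, PHQ-9, GAD-7 and PHQ-PD at 3 months would give some indication of an early effect that fades.

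None of this supplies a reason for leaving a short form out of a mailing that already goes out.

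**Conclusion.** The point holds as a cheap improvement to the measurement schedule, not as a demonstrated bias. If effects are expressed as QALYs, the use that section 8.3 describes for this instrument, the incremental QALY lacks the term 0.25 x [d3 - (d0 + d6)/2]. Across the assumed paths the plan's error runs from about 43% understatement to about 20% overstatement, with zero for a linear course to month 6. Which of these applies is unknown, because the protocol gives no utilities. Only the secondary economic objective is touched. The primary DHI analysis has its own 3-month measurement, and two follow-up points for a secondary quality-of-life outcome are not in themselves a defect.

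**What to change.** In the overview of measurements (section 8.3), mark the EQ-5D-5L at 3 months for the intervention study and add the form to the existing 3-month questionnaire for groups B and C. Where effects are expressed as QALYs, use the values at 0, 3, 6 and 12 months in the calculation and say so in section 10.2.

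The cost, by the protocol's own estimate for the form, is several extra minutes once for each of 250 patients. No mailing or visit is added. The change has to be in place before patients reach month 3, because a value not collected then cannot be recovered.

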#### II. Intervention study

We will perform both intention-to-treat and per-protocol analysis. We will use univariate and multivariate analyses to compare outcomes of usual care and intervention group. To investigate the effectiveness of the risk factor-guided intervention, we will use a repeated-measures mixed-effect (RMME) model to assess differences in the 1-year DHI score change, adjusted for potential confounders.

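### The cost-effectiveness effect is named as the EQ-5D-5L, with no statement of QALYs or of adjustment for baseline utility, so the unit behind the planned ceiling ratios and net monetary benefits is not fixed

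*Protocol*

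**What the plan says.** Cost-effectiveness is the third secondary objective (Protocol section 2). Section 10.2 sets out its analysis:

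- Effect: "The effect measure that will be used for the cost-effectiveness is EQ-5D-5L". No visit, change score, utility or QALY is named.
- Ratio: the cost contrast between arms is the numerator. The denominator is worded as "treatment groups by the difference in mean effects between the treatment groups", and nothing is said about adjustment.
- Decision analysis: "Cost-effectiveness acceptability curves and net monetary benefits will also be calculated". The curves are to be drawn "for a range of different ceiling ratios thereby showing decision uncertainty". The unit of effect to which a ceiling ratio applies is not given.

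The only mention of QALYs is in section 8.3, in the description of the questionnaires, where the instrument "is often used to translate the effect of an intervention into Quality Adjusted Life Years". That describes a common use of the instrument and is not an analysis step of this trial.

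The overview table in section 8.3 schedules the EQ-5D-5L in the intervention study at baseline, 6 and 12 months, and not at 3 months.

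On adjustment, section 10.1 (II) plans a mixed-effect model for the DHI "to assess differences in the 1-year DHI score change, adjusted for potential confounders". Section 10.2 takes quality of life into the univariate and multivariate analyses as a clinical outcome. Neither statement is linked to the cost-effectiveness ratio.

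**The concern.** Net monetary benefit multiplies the effect by a money value per unit of effect, so the unit must be known. An EQ-5D-5L score at one visit has no time dimension, whereas a QALY is that score accumulated over time. If the analyst follows the sentence as written and divides by a difference in scores, the result is a cost per index point. A reader who sets it beside a per-QALY ceiling ratio would be comparing two different scales.

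The second issue is baseline utility. Practices are randomised before patients are included (section 8.2). GPs are told their allocation and also identify patients (section 11.2). A difference in baseline utility between arms is therefore plausible, by chance or through recruitment. If the effect is a raw difference in means, part of that difference enters the denominator of the ratio. The baseline value that would correct for it is already collected.

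**Working it through.** The protocol gives no figure for the economic evaluation (no utility SD, ceiling ratio or expected effect), so there is none to reproduce. The steps below show what the open wording allows.

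**1. Index difference against QALY difference**

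Inputs: visits at 0, 0.5 and 1 year (overview table, section 8.3). Let d0, d6 and d12 be the between-group utility differences at those visits. By the trapezoid rule:

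QALY difference = 0.25 × (d0 + d6) + 0.25 × (d6 + d12) = 0.25 × d0 + 0.5 × d6 + 0.25 × d12

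With d0 = 0 and d12 = D:

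| Course of the effect | d6 | QALY difference |
|---|---|---|
| Appears only at 12 months | 0 | 0.25 D |
| Linear | 0.5 D | 0.25 D + 0.25 D = 0.50 D |
| Complete by 6 months | D | 0.5 D + 0.25 D = 0.75 D |

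In these three cases the cost per 12-month index point is 25% to 75% of the cost per QALY. With an assumed cost difference of 500 and D = 0.05, it is 500/0.05 = 10,000 per index point. Per QALY it is 500/0.0125 = 40,000, 500/0.025 = 20,000 and 500/0.0375 = 13,333.

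**2. When the direction reverses**

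The QALY difference exceeds d12 when 0.5 × d6 + 0.25 × d12 > d12, that is, when d6 > 1.5 × d12. Example with d6 = 0.05 and d12 = 0.02: QALY difference = 0.025 + 0.005 = 0.03. At the same assumed cost difference, this is 500/0.02 = 25,000 per index point against 500/0.03 = 16,667 per QALY. The index ratio now looks worse. An effect that fades is conceivable here: exercise therapy lasts eight weeks, and the first three stepped-care steps are set at 6 weeks each, 18 weeks in all (section 5.1).

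**3. Baseline utility imbalance**

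Inputs from the protocol: 125 per arm; design effect 1 + (5 − 1) × 0.05 = 1.2 (section 4.4). Assumed: utility SD 0.15 to 0.25; correlation r of 0.5 to 0.7 between baseline and each follow-up utility, with equal SDs at all visits.

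SE of the baseline difference = SD × √(2 × 1.2/125) = SD × 0.1386

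- SD 0.15: 0.021
- SD 0.25: 0.035

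A baseline difference b carries an expected r × b into each follow-up difference, so an unadjusted QALY difference shifts by b × (0.25 + 0.5 r + 0.25 r) = b × (0.25 + 0.75 r).

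- r = 0.5: factor 0.625, and 0.0208 × 0.625 = 0.013
- r = 0.7: factor 0.775, and 0.0346 × 0.775 = 0.027

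For an unadjusted 12-month index difference the shift is r × b: 0.5 × 0.0208 = 0.010 to 0.7 × 0.0346 = 0.024.

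Against the illustrative effects in step 1 (0.0125 to 0.0375 QALY), a shift of 0.013 to 0.027 is of the same order.

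**The case against.** The strongest reply is that the sentence in section 10.2 is shorthand. Section 8.3 connects the instrument with QALYs, the visit schedule suits a QALY calculation, and net monetary benefit is normally computed on QALYs. The value set, QALY method and covariates may stand in an analysis plan that is not shown. This is a fair account of what the sponsor may have meant, and silence on those details is not in itself a fault. But section 10.2 does not leave the effect measure open. It fixes it, and it fixes it as an instrument and not as a quantity with a unit.

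Three stronger readings are tempting, and the protocol does not support them:

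- *That the protocol commits to an unadjusted difference.* It does not say so. A difference in mean effects could come from an adjusted model.
- *That ceiling ratios cannot be used at all.* They can be defined per unit of any effect, and section 10.2 names no per-QALY threshold. Only comparison with a per-QALY ceiling ratio fails.
- *That the ratio would always look too favourable.* This assumes that the effect is the 12-month index difference, a visit section 10.2 does not name, and that the gain does not peak early and fade. If the effect were the time-weighted mean utility over the year, it would equal the QALY numerically and nothing would be distorted.

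It is also fair to say that an unadjusted interval already reflects chance imbalance, so adjustment for chance alone mainly gains precision. Imbalance caused by GPs recruiting with knowledge of their allocation is different: it would be bias that the interval does not cover. The protocol gives no basis for quantifying it.

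**Conclusion.** The concern holds as a defect of specification in a secondary objective. The effect has no stated unit suited to the planned decision analysis, and adjustment for baseline utility is not stated in a design where imbalance is plausible.

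On the literal reading as a 12-month index difference with no baseline difference, the QALY difference is 0.25 to 0.75 of the index gain for the late, linear and early-and-sustained courses, and exceeds it once d6 > 1.5 × d12. The direction therefore cannot be stated in advance. The carry-over of 0.013 to 0.027 QALY for a one-SE imbalance rests on the assumed SDs and correlations and on the effect being taken as a raw difference. Only 62.5% to 77.5% of the imbalance carries over, not all of it.

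The primary DHI analysis is unaffected.

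**What to change.** Replace the sentence on the effect measure in section 10.2 with wording such as:

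> The effect measure is the QALY over 12 months, calculated as the area under the EQ-5D-5L utility curve at 0, 6 and 12 months. The between-group QALY difference is adjusted for baseline utility by regression within each bootstrap replicate.

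State in the same place that ceiling ratios and net monetary benefits are expressed per QALY. The value set can stay in the analysis plan.

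The cost is a wording change and one regression step inside the bootstrap already planned. All three EQ-5D-5L measurements are already scheduled, so no visit, questionnaire or patient is added. If QALYs were intended from the start, the change only records that.
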